### Intervention Implementation

The REACH TBI intervention will be carried out by a postdoctoral fellow interventionist who will be trained with didactic and hands-on content, knowledge assessment, skills practice, and role-playing for certification. Interventionist training includes strategies for overcoming problems associated with telephone interactions such as decreased cues and technological difficulties. The interventionist will use a mock caregiver to complete a role play of 2 key areas of the intervention: Target Concern Plan and Cognitive Reframing [43]. The Certification Role Play Observation Checklist for Individual Sessions used by the caregiver center will be used for the role play. The checklist includes behaviorally anchored ratings of specific procedural techniques (eg, correct use of forms) and clinical skills (eg, active listening). Performances will be observed for content and process. Feedback will be individually provided for each of the items listed on the checklist. The structure of the feedback will include positive behavior demonstrated; what behaviors should have occurred or occurred and were not in keeping with the protocol; and the rationale for the behavior that was expected. To assess intervention benefits accurately, early sessions for each interventionist will be monitored by study investigators, with caregiver permission. The investigators will provide feedback to the interventionist immediately after each session, focusing on fidelity, interventionist delivery, and evidence of caregiver receipt and enactment.

### Intervention

REACH TBI will be delivered by telephone in 6 individual hour-long sessions over 3 months, about every 2 weeks by a trained and certified interventionist. The REACH TBI sessions incorporate evidence-based components that have been shown to be crucial to successful caregiving interventions including problem-solving, cognitive reframing, and stress management [35]. The interventionist and caregiver negotiate the concerns to be addressed using those identified by the risk assessment [26,36]. Using problem-solving techniques, the interventionist and caregiver attempt to find effective and workable solutions to a specific target concern that is causing strain and stress for the caregiver, using the Caregiver Notebook. The target concern could be something related to the caregiver, such as asking family members for help, or to the care recipient such as bathing or driving. In this way, the intervention accommodates whatever concern the caregiver is experiencing—from activities of daily living or instrumental activities of daily living challenges to caregiver stress, guilt, or grief.

Each session is structured to build on the previous session using the protocol. Although tasks are structured and predetermined (eg, problem-solving), the focus of the task is a risk area (eg, safety), concern (eg, lack of support), or patient problem (eg, angry outbursts) that the caregiver has identified as troubling. One of the main foci of REACH is problem-solving. The interventionist teaches the ABC (Antecedent, Behavior, Consequences) method of problem-solving, and the caregiver and interventionist identify action-oriented behavioral strategies to address caregiving problems or V/SM behaviors using topics from the Caregiver Workbook in a Targeted Concern Plan. An outline of the intervention can be seen in Table 1.

**Table 1 table1:** Outline of the REACH^a^ TBI^b^ intervention.

REACH TBI session or topic	Overview of content and structure
Assessment and session 1: stress management	Caregiver assessment Introduce intervention and review Caregiver Notebook Discuss stress Introduce stress management technique, signal breath
Session 2: problem-solving	Introduce session Review or modify the last session commitment, signal breath Provide general information about the Veteran or Service Member’s health condition Present safety material Introduce health care issues and health guide Problem-solve—target concern #1
Session 3: cognitive reframing	Review the health guide and safety Review or modify problem-solving plan #1 Make commitment for problem-solving plan #1 Introduce cognitive reframing
Session 4: problem-solving or cognitive reframing or stress management	Review the health guide and safety Determine caregiver goal attainment for cognitive reframing and review or modify, if needed Review or modify problem-solving plan #1 Determine caregiver goal attainment for problem-solving plans and review or modify, if needed If appropriate, identify target concern #2 Introduce problem-solving plan #2 or Work on cognitive reframing thought record
Session 5: problem-solving, cognitive reframing, stress management	Review the health guide and safety Determine caregiver goal attainment for any problem-solving plans and review or modify Review or modify cognitive reframing Offer stress management technique
Session 6 and Closure: problem-solving, stress management, and cognitive reframing review	Review Caregiver Notebook Review safety recommendations Review health and use of health guide Review caregiver well-being Review stress management techniques and strategies that worked Review cognitive reframing techniques Review problem-solving plans covered and strategies that worked

^a^REACH: Resources for Enhancing All Caregivers’ Health.

^b^TBI: traumatic brain injury.

### Data Collections

#### Quantitative Data Collection

Demographic and baseline data will be collected either by telephone or Qualtrics (Qualtrics International Inc) after enrollment and before randomization. Baseline data collection includes validated measures of key TBI caregiver outcomes such as strain, depression, anxiety, self-efficacy, and health care frustration. Follow-up data will be collected at 3 and 6 months from all participants and at 9 months from waitlist control participants using the same validated measures as during the baseline data collection. The study timeline is illustrated in Figure 1.

**Figure 1 figure1:**
[figure not shown]
Waitlist control clinical trial timeline. REACH: Resources for Enhancing All Caregivers’ Health; TBI: traumatic brain injury.

#### Qualitative Data Collection

A qualitative telephone exit interview will be conducted with all participants at the 3-month follow-up, after their last session, to evaluate their experiences using REACH TBI with a focus on caregiver satisfaction, usefulness, benefits, challenges, and implementation.

### Data Management

ID numbers will be used for all participants rather than participant names. Once analytic files are cleaned, all identifiable private information associated with an individual will be deleted from the analytic files, and analysis will be limited to data that are identified by an ID. Authorized project staff members will be assigned an active, unique user identification code and password to the server or network containing the data. The outcome measures will be compiled into a single survey format in Qualtrics and collected at baseline, 3, and 6 months from all participants and at 9 months from waitlist control participants.

### Outcome Measures

TBI Caregiver Quality of Life Caregiver Strain-short form 6a assesses caregiver strain [44]. A total of 6 items are scored from 1 (never) to 5 (always), with higher scores indicating greater strain. Among caregivers of V/SMs with TBI, internal consistency is α=.88, test-retest reliability is *r*=0.80, and convergent validity with mental health is *r*=–0.54 [45].

PROMIS (Patient-Reported Outcomes Measurement Information System) Emotional Distress—Depression—short form 8a assesses caregiver depression [46]. A total of 8 items are scored from 1 (never) to 5 (always). Scores range from 8 to 40 with higher scores indicating greater depression. Among caregivers of V/SMs with TBI, internal consistency is α=.94, test-retest reliability is *r*=0.70, and convergent validity with mental health is *r*=–0.73 [45].

PROMIS Emotional Distress—Anxiety—short form 8a assesses caregiver anxiety [46]. A total of 8 items are scored from 1 (never) to 5 (always). Scores range from 8 to 40 with higher scores indicating greater anxiety. Among caregivers of V/SMs with TBI, internal consistency is α=.89, test-retest reliability is *r*=0.65, and convergent validity with mental health is *r*=–0.66 [45].

PROMIS General Self-Efficacy assesses caregiver self-efficacy [47]. A total of 10 items are scored from 1 (I am not at all confident) to 5 (I am very confident), with higher scores indicating greater self-efficacy. Internal consistency is α=.94, and convergent validity with optimism is *r*=0.58 [47].

TBI-Caregiver Quality of Life Health Care Frustration—Self—short form 6a assesses frustrations a TBI caregiver has had with health care services [48]. A total of 6 items are scored from 1 (not at all) to 5 (very much), with higher scores indicating greater frustration with services received. Among caregivers of V/SMs with TBI, internal consistency is α=.96, test-retest reliability is *r*=0.89, and convergent validity with caregiver strain is *r*=0.60 [48].

### Data Analysis

#### Preliminary Analyses

Descriptive statistics will be computed for the total sample and stratified by treatment group for baseline participant characteristics. Means and SD (or medians and IQR) or counts and proportions will be calculated for continuous and categorical variables, respectively. In addition, an analysis of missing data will be conducted to examine factors that may be associated with the likelihood of missing data. Any factor found to be associated with the likelihood of missing data will be included in the final model.

Once assigned to a study arm, participants will be considered in the study, and we will follow an intention-to-treat approach (see below for details). Primary outcomes are measured for all participants at baseline, at 3 months, and after 6 months (or 9 months for the waitlist control group). We estimate the necessary sample size based on comparing groups at 3 months post randomization using baseline scores as a covariate.

#### Primary Quantitative Analyses

The intention-to-treat principle will be applied to all analyses. Once a participant is assigned to a treatment group, they will be included in the group in all analyses even if they end treatment or are lost to follow-up. Parallel analyses will be completed for each outcome. A linear mixed effects model [41] will be used to test the effectiveness of the REACH TBI intervention compared to a waitlist control initially for the primary outcome of caregiver strain. Contrasts will be coded to allow for tests of the mean difference between groups at 6 months postintervention and 3 months postintervention with 3-month measurements as the primary outcome. Each participant’s baseline score on the outcome will be included in the model in addition to a random intercept and fixed effects of treatment, time, and the treatment-by-time interaction. To account for multiple testing, Hochberg’s step-up procedure will be used to control the false discovery rate to .05. All analyses will be completed using the lme4 package [49] in the R statistical software (version 4.4.0; R Core Team).

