#### Secondary Quantitative Analyses

Parallel analyses to those described in the primary analysis section will be completed for all secondary outcomes (eg, depression, anxiety, self-efficacy, and military health care frustration). In addition, group means will be compared at 6 months post randomization. Given that both groups will have been exposed to the intervention at this point, no difference between groups is expected. Finally, pairwise change within each group (eg, baseline vs 3 months and baseline vs 6 months within the control group) will be tested [41]. We expect that the treatment group will show improvement from baseline to 3 and 6 months post randomization but not between 3 and 6 months. For the control group, it is anticipated there will be no improvement or worsening between baseline and 3 months post randomization but will show improvement for comparisons of baseline and 3 months with 6 months post randomization.

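### The random-intercept model pools the month-3 and month-6 variances, so the size of the primary 3-month test depends on an equality that the trial does not need to assume

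*Protocol article*

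**What the plan says.** All places are in the protocol article.

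- **Primary Quantitative Analyses** sets out one linear mixed model for caregiver strain, specified as "baseline score on the outcome will be included in the model in addition to a random intercept and fixed effects of treatment, time". A treatment-by-time term is also listed. The random part is an intercept only.
- The same section asks this model for "tests of the mean difference between groups at 6 months postintervention and 3 months postintervention". It makes month 3 the primary time point: "with 3-month measurements as the primary outcome". I take these to be the 3- and 6-month visits after randomization, as in the other sections.
- It names the software: "All analyses will be completed using the lme4 package".
- **Quantitative Data Collection** gives the visits: "Follow-up data will be collected at 3 and 6 months from all participants and at 9 months from waitlist control participants".
- **Secondary Quantitative Analyses** describes month 6: "Given that both groups will have been exposed to the intervention at this point, no difference between groups is expected".
- **Preliminary Analyses** gives the basis of the sample size: "We estimate the necessary sample size based on comparing groups at 3 months post randomization using baseline scores as a covariate".

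The article mentions no visit-specific variance, unstructured covariance or robust standard error for this model, and reports no standard deviation at either visit.

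**The concern.** A random intercept plus a single residual variance gives every visit the same total variance. With two follow-up visits, the variance used for the 3-month contrast is estimated from both of them. If the month-6 variance is smaller than the month-3 variance, the primary standard error is too small and the type I error exceeds 5%. If it is larger, the standard error is too large and power is lost.

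The design does not guarantee equality, for two reasons. One arm has been treated by month 3 and both by month 6, so any effect of treatment on the spread of scores acts on one arm at the first visit and on both at the second. The correlation with baseline may also fall with time, which leaves more residual variance at month 6.

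At stake are the primary p-value and confidence interval, and the match between the analysis and a sample size that used the 3-month variance only.

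**Working it through.** **Inputs from the article** (Participants, Recruitment, and Sample Size): 55 per arm, d = 0.50, correlation of pre- and post-intervention scores 0.50, two-sided alpha 0.05, 80% power, 10% attrition.

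**Inputs assumed:** k = V6/V3, the ratio of month-6 to month-3 variance given baseline, and the correlation between the two follow-up residuals in the simulations.

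**1. The plan's own figure.** ANCOVA at 3 months has residual SD sqrt(1 − 0.5²) = 0.866. The normal formula gives n = 2 × 0.75 × (1.960 + 0.842)² / 0.5² = 47.1, so 48 per arm, and 48/0.9 rounds up to 54. The noncentral t gives 49 per arm, and 49/0.9 rounds up to 55. The stated 55 per arm reproduces.

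**2. Standard error under the planned model.** Let C be the covariance of the two visits given baseline. The 3-month contrast is the contrast in the two-visit mean minus half the contrast in the change (month 6 minus month 3). With complete data the random-intercept model treats these two parts as independent:

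- model: (2/n) × [(V3 + V6 + 2C)/4 + (V3 + V6 − 2C)/4] = (2/n) × (V3 + V6)/2
- truth: subtract the covariance of mean and change, (V6 − V3)/2, which leaves (2/n) × V3

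So SE(model)/SE(true) = sqrt((1 + k)/2), whatever the value of C.

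**3. Size.** With 55 × 0.9 = 49.5 completers per arm, the true SE is 0.866 × sqrt(2/49.5) = 0.174, and 0.5/0.174 = 2.87. Writing f for the SE ratio, type I error = 2 × [1 − Φ(1.96 f)] and power = Φ(2.87 − 1.96 f).

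| k (assumed) | f | type I error | power |
|---|---|---|---|
| 0.67 | 0.914 | 7.3% | 86% |
| 0.8 | 0.949 | 6.3% | 84% |
| 0.9 | 0.975 | 5.6% | 83% |
| 1 | 1.000 | 5.0% | 82% |
| 1.12 | 1.030 | 4.4% | 80% |
| 1.25 | 1.061 | 3.8% | 79% |
| 1.5 | 1.118 | 2.8% | 75% |

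**4. Checks.** Simulation with 50 per arm and follow-up correlation 0.5 gave type I error 7.1%, 6.2%, 5.0%, 3.8% and 2.9%, and power 85%, 84%, 81%, 77% and 74%, at k = 0.67, 0.8, 1, 1.25 and 1.5. The visit-specific analysis stayed at 4.9–5.2% and 81%. Mixed models fitted to large simulated data sets gave SE ratios of 0.911 and 1.095 at SD ratios 0.8 and 1.2, against 0.906 and 1.105 from the formula.

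**5. What the values of k require.**

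- *Correlation with baseline falls, raw variances equal:* k = (1 − r6²)/0.75. A month-6 correlation of 0.4 gives 0.84/0.75 = 1.12; 0.3 gives 0.91/0.75 = 1.21; zero gives 1.33. This route alone cannot reach 1.5.
- *Treatment multiplies an arm's variance by c:* k = 2c/(1 + c). c = 0.8 gives 0.89 (type I error 5.7%) and c = 1.2 gives 1.09 (4.5%). Reaching 0.67 needs treatment to halve the variance; reaching 1.5 needs it to triple.

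A range of about 0.9 to 1.2 is therefore the plausible one; 0.67 and 1.5 are extremes.

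**The case against.** The strongest reply is that the harm is hypothetical. At k = 1 the analysis is exact, and nothing in the article suggests unequal variances. A baseline-adjusted random-intercept model is a common choice for two follow-ups at N = 110. SD differences of about 10% move the type I error only to about 4–6%. The two mechanisms can also partly cancel: decaying correlation pushes k above 1, while a treatment that narrows the spread pushes it below. Diagnostics and sensitivity models are normally left to the SAP. All of this stands, and it makes the point a minor one. It does not remove the point, because the article itself fixes both the random part and lme4, whose linear mixed model has one residual variance.

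A reader might infer three stronger things that the documents do not support.

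- *That the primary test is invalid or anti-conservative.* Neither the size nor the direction of any error can be read from the article. If residual variance grows with time, the test is conservative.
- *That the absence of an expected group difference at month 6 dilutes the 3-month effect.* The model includes treatment-by-time, so the month-6 mean difference does not enter the 3-month contrast. Only variance is shared.
- *That the sample size is wrong or contradicts the model.* It reproduces, and it agrees with the planned model at k = 1.

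The formula is exact only for balanced, complete data. If more data are missing at month 6 than at month 3, month 3 weighs more in the pooled variance and the error shrinks.

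**Conclusion.** The point holds as a modest weakness in the analysis choice. The planned model makes the primary 3-month standard error depend on the variance at a visit after crossover, through the factor sqrt((1 + k)/2). The point estimate is unbiased with complete data. For k between about 0.9 and 1.2, the type I error lies between about 5.6% and 4.0%, and power is at most about 3 points below its value at k = 1. At k = 1.25 power is 77–79%, depending on whether simulation or the normal approximation is used. These figures rest on assumed variance ratios, near-complete data, and the article's own d = 0.50 and baseline correlation of 0.50. The case for changing the model is that the assumption can be dropped at almost no cost.

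**What to change.** Replace the random intercept with an unstructured covariance over months 3 and 6, for example with R mmrm or nlme::gls. Keep baseline, treatment, time and treatment-by-time, preferably add baseline-by-time, and read the primary 3-month contrast from that model. A 3-month ANCOVA adjusted for baseline, which is the sample-size basis, would also serve as the primary test. Fix the choice before outcomes are analysed, since the direction of any error is not known in advance.

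Cost: a different R package, one extra variance parameter, one extra fixed effect if baseline-by-time is added, and the same change in the parallel secondary-outcome and moderation models. No new data and no change in sample size are needed.

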#### Secondary Quantitative Analyses

Parallel analyses to those described in the primary analysis section will be completed for all secondary outcomes (eg, depression, anxiety, self-efficacy, and military health care frustration). In addition, group means will be compared at 6 months post randomization. Given that both groups will have been exposed to the intervention at this point, no difference between groups is expected. Finally, pairwise change within each group (eg, baseline vs 3 months and baseline vs 6 months within the control group) will be tested [41]. We expect that the treatment group will show improvement from baseline to 3 and 6 months post randomization but not between 3 and 6 months. For the control group, it is anticipated there will be no improvement or worsening between baseline and 3 months post randomization but will show improvement for comparisons of baseline and 3 months with 6 months post randomization.

#### Exploratory Quantitative Analyses

A moderation analysis [50] will be completed to examine how disability level and V/SM health conditions impact the effect of the intervention. Each variable and its interaction with treatment will be added separately to the linear mixed effects models described in the primary analyses section. If statistically significant interactions are found, results will be reported with the mean treatment effect, and ±1 SD on the moderator to improve results interpretability.

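### The exploratory moderation model names no moderator-by-treatment-by-time term, so its moderation estimate mixes the 3-month effect with a 6-month contrast in which both arms have been exposed to REACH TBI

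*Protocol article*

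**What the plan says.** All places are in the protocol article.

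- **Primary Quantitative Analyses.** Each outcome is analysed with a linear mixed model that has the baseline score as covariate, "in addition to a random intercept and fixed effects of treatment, time, and the treatment-by-time interaction". Contrasts give "tests of the mean difference between groups at 6 months postintervention and 3 months postintervention with 3-month measurements as the primary outcome".
- **Secondary Quantitative Analyses.** On group means at 6 months post randomization: "Given that both groups will have been exposed to the intervention at this point, no difference between groups is expected". The early arm is expected to improve by 3 months and not to change between 3 and 6 months.
- **Exploratory Quantitative Analyses.** The aim is to "examine how disability level and V/SM health conditions impact the effect of the intervention". On the model: "Each variable and its interaction with treatment will be added separately to the linear mixed effects models described in the primary analyses section". If an interaction is significant, "results will be reported with the mean treatment effect, and ±1 SD on the moderator". The section names no interaction of the moderator with time and no visit for the moderation contrast.
- **Quantitative Data Collection.** "Follow-up data will be collected at 3 and 6 months from all participants and at 9 months from waitlist control participants".

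The primary section dates its contrasts from the intervention. The preliminary and secondary sections count from randomization, which fits the visit schedule. I use time from randomization.

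**The concern.** Only the 3-month visit compares caregivers who have had REACH TBI with caregivers who have not. At 6 months the comparison is early against delayed exposure. The protocol respects this for the average effect by including treatment-by-time and making 3 months primary. It does not carry the separation into the moderation analysis, where the listed terms leave one moderator-by-treatment coefficient common to both visits.

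The analysis is meant to show for whom the intervention works. If moderation is present at 3 months and has faded between the arms by 6 months, the coefficient understates it and the test loses power. The effects at the mean and ±1 SD of the moderator are also tied to no visit, although the model has a different average effect at each.

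**Working it through.** **The plan's own figure.** The article gives no figure for moderation, only the sample size for the 3-month comparison: d = 0.50, pre-post correlation 0.50, two-sided 0.05, 80% power, 10% attrition. The residual SD is √(1 − 0.5²) = √0.75 = 0.866. The normal approximation gives 48 per arm, or 54 after attrition. The noncentral t gives 49 per arm (power 0.808), and 49/0.9 = 54.4, so 55. The stated 55 per arm is reproduced and is not in question.

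**What the coefficient estimates.** Let g3 and g6 be the between-arm difference in moderator slope at 3 and 6 months, in outcome SD per moderator SD. The moderator does not vary within a person. With complete data and a random intercept, the two visits get equal weight in a time-constant interaction:

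coefficient = (g3 + g6)/2

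The coding of time does not matter, because treatment-by-time frees only the mean effect.

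| Situation at 6 months | g6 | Coefficient |
|---|---|---|
| Waitlist arm responds as the early arm did, early arm keeps its gain | 0 | 0.50 g3 |
| Waitlist arm reaches half the moderated response | 0.5 g3 | 0.75 g3 |
| No catch-up | g3 | 1.00 g3 |

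If the waitlist-only 9-month record also entered the model, the waitlist slope would average (0 + 1 + 1)/3 = 2/3 of g3 against 1 in the early arm, leaving about 0.33 g3.

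**Missing 6-month data, g6 = 0.** Let m be the fraction missing at 6 months and ρ the residual correlation between visits (not stated; assumed 0.2 to 0.7). A completer carries weight 2/(1+ρ) and a person with 3 months only carries weight 1, so

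coefficient/g3 = [(1−m)/(1+ρ) + m] / [2(1−m)/(1+ρ) + m]

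- m = 0.10, ρ = 0.2: (0.75 + 0.10)/(1.50 + 0.10) = 0.53. With ρ = 0.7 it is 0.54.
- m = 0.20, ρ = 0.2: (0.667 + 0.20)/(1.333 + 0.20) = 0.57. With ρ = 0.7 it is 0.59.

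Generalised least squares on 6,000 generated records gave 0.53 to 0.54 and 0.56 to 0.58, the same apart from sampling noise.

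**Power, g6 = 0, complete data.** With 99 analysed (110 × 0.9), the standard error of the 3-month moderation is 2 × 0.866/√99 = 0.174. The moderation detectable with 80% power is 2.80 × 0.174 = 0.49. The time-constant coefficient has standard error 0.174 × √((1+ρ)/2), which is 0.77 to 0.92 of the 3-month one, so the test loses less than the estimate does. Power is 1 − Φ(1.96 − 0.5 × 0.488/SE):

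| ρ | SE | Power |
|---|---|---|
| 0.2 | 0.135 | 44% |
| 1/3 | 0.142 | 40% |
| 0.5 | 0.151 | 37% |
| 0.7 | 0.160 | 33% |

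The value 1/3 follows if all pairwise correlations are 0.50: (0.50 − 0.25)/0.75.

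**Simulation checks.** The true moderation sizes here are assumed.

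- 2,000 trials per scenario, 49 per arm, month 3 to 6 correlation 0.6, complete data, g6 = 0. For a true 0.50, the model as written gave 0.253 with 37% power, and the time-specific model gave 0.503 with 78%. For a true 0.30, the figures were 0.150 with 16% and 0.298 with 37%.
- 300 trials, N = 110, 10% missing at 6 months, true −0.50. The model as written gave −0.27 with 47% power. The model with the three-way term gave −0.51 with 86%.

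**The case against.** **The article does not exclude a three-way term.** Treatment also enters the primary model through its interaction with time, so adding a moderator's interaction with treatment could be read as crossing it with both treatment terms and keeping the 3-month contrast. That reading is possible, and a fuller analysis plan may adopt it. It is not the plain one. The article lists the terms to be added, and a programmer following the list would fit the time-constant version. This is therefore a stated rule that gives a diluted answer, not just a detail left out.

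**Halving is not established.** This stands. A reader might infer from the 6-month statement that no between-arm moderation is expected then, so the coefficient must be half. The protocol expects equality of group means and is silent on moderation. Zero moderation follows only if the waitlist arm responds to the moderator as the early arm did and the early arm keeps its gain.

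**Published ±1 SD effects would not simply be half their true spread.** This also stands. A reader might infer it, but 0.5 is the expected value before selection. These effects are reported only after a significant interaction, which favours large estimates. Back-solving from the first simulation gives a standard error of about 0.155, and the mean significant estimate is then about 0.41 for a true 0.50 and 0.38 for a true 0.30.

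**The primary model does not pool the two visits.** Correct. Treatment-by-time keeps the average effects visit-specific, and only the moderation term is common to both. The analysis is exploratory, and no sample size or primary test depends on it. If there is no moderation at either visit, the interaction test is not invalidated.

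**Conclusion.** The point holds as a defect in how the exploratory moderation model is specified. As listed, the model estimates the average of the 3-month and 6-month moderation, whereas the protocol's question concerns the effect of the intervention, which only the 3-month comparison of exposed with unexposed caregivers isolates. It recovers the 3-month moderation only if the 6-month moderation is the same, which fits poorly with a waitlist arm expected to have caught up on average.

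The size depends on catch-up: from 0.5 of the 3-month value with full catch-up to 1.0 with none. In the full catch-up case power falls from 80% to between 33 and 44%. These figures rest on a random-intercept model, 3- and 6-month records only, and an assumed residual correlation of 0.2 to 0.7. The consequence is a diluted, less powerful moderation analysis that leans towards finding none. The primary test and the sample size are unaffected. It should be corrected, with the weight due to an exploratory analysis.

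**What to change.** In Exploratory Quantitative Analyses, add moderator-by-time and moderator-by-treatment-by-time to each moderation model. State that moderation is tested as the moderator-by-treatment contrast at 3 months post randomization. Fitting the moderation model to the 3-month data alone would also serve. State that the effects at the mean and ±1 SD of the moderator are 3-month effects. If the three-way term is already intended, one sentence settles it.

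The cost is two extra terms per moderator and a standard error about 1.08 to 1.29 times that of the time-constant coefficient (1/0.92 to 1/0.775). No new data or participants are needed. Whether to report these effects regardless of significance is a separate choice and does not bear on this defect.
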